## Abstract

**Background:**

The foreskin is the main site of HIV acquisition in a heterosexual uncircumcised man, but many men in endemic countries are reluctant to undergo penile circumcision (PC). Observational studies suggest that proinflammatory anaerobic bacteria are enriched on the uncircumcised penis, where they may enhance HIV susceptibility through increased foreskin inflammatory cytokines and the recruitment of HIV-susceptible CD4^+^ target cells. This trial will examine the impact of systemic and topical antimicrobials on ex vivo foreskin HIV susceptibility.

**Methods/design:**

This randomized, open-label clinical trial will randomize 125 HIV-negative Ugandan men requesting voluntary PC to one of five arms (*n* = 25 each). The control group will receive immediate PC, while the four intervention groups will defer PC for 1 month and be provided in the interim with either oral tinidazole, penile topical metronidazole, topical clindamycin, or topical hydrogen peroxide. The impact of these interventions on HIV entry into foreskin-derived CD4^+^ T cells will be quantified ex vivo at the time of PC using a clade A, R5 tropic HIV pseudovirus assay (primary endpoint); secondary endpoints include the impact of antimicrobials on immune parameters and the microbiota of the participant’s penis and of the vagina of their female partner (if applicable), assessed by multiplex enzyme-linked immunosorbent assay and 16S rRNA sequencing.

**Discussion:**

There is a critical need to develop acceptable, simple, and effective means of HIV prevention in men unwilling to undergo PC. This trial will provide insight into the causative role of the foreskin microbiota on HIV susceptibility, and the impact of simple microbiota-focused clinical interventions. This may pave the way for future clinical trials using low-cost, nonsurgical intervention(s) to reduce HIV risk in uncircumcised heterosexual men.

**Trial registration:**

ClinicalTrials.gov, NCT03412071. Retrospectively registered on 26 January 2018.

**Electronic supplementary material:**

The online version of this article (10.1186/s13063-019-3545-7) contains supplementary material, which is available to authorized users.

## Background

The provision of early and effective antiretroviral therapy for a person infected with HIV reduces the risk of transmission to their partner to negligible levels, and consistent use by an uninfected person of pre-exposure prophylaxis (PrEP) reduces their risk of HIV acquisition by 90–95% [1, 2]. However, the global rate of new HIV infections outstrips current treatment capacity, and the ability and political will to fund expansion of PrEP programs in endemic countries is not clear; furthermore, the emergence of viral resistance in sub-Saharan Africa is a real concern [3, 4]. Safe penile circumcision (PC) reduces HIV susceptibility by almost 60% in heterosexual men and is being actively implemented in 14 priority sub-Saharan African countries where infant circumcision has not been the cultural norm [5–7]. Nonetheless, many eligible men choose not to undergo this surgical procedure, and PC implementation is falling well short of global targets [8, 9]. Based on the key role of the foreskin in HIV acquisition [10], new nonsurgical prevention tools that are acceptable to men who choose to remain uncircumcised could enhance prevention efforts.

## Foreskin inflammation associated with penile anaerobes increases HIV risk

Although the immunopathogenesis of HIV acquisition in the foreskin is poorly understood, observational studies have demonstrated strong immune and microbial associations of HIV acquisition that suggest new avenues for prevention. Specifically, foreskin tissues are enriched for highly HIV-susceptible CD4^+^ T cell subsets, including T helper 17 (Th17) cells and CD4^+^ T cells expressing the HIV coreceptor CCR5 [11], and these highly susceptible CD4^+^ T cell subsets were reduced in the foreskins of HIV-exposed but seronegative men [12]. This suggests that foreskin inflammation and/or immune activation enhances HIV susceptibility and, in keeping with this, prepuce levels of the chemotactic cytokine interleukin-8 (IL-8) were directly associated with an increased risk of HIV acquisition in Ugandan men, and correlated with an increased tissue density of HIV-susceptible CD4^+^ subsets [13]. Interestingly, these immune parameters also strongly correlated with the density of gram-negative anaerobic bacteria, such as *Prevotella* spp., in the foreskin prepuce [13–15], and PC has been previously shown to reduce the prevalence of these penile bacteria [16].

## Hypothesis

Based on these observations, we hypothesize that host immune alterations induced in the uncircumcised penis by gram-negative anaerobic bacteria enhance HIV susceptibility, and that oral and/or topical antimicrobials will reduce foreskin anaerobe load, local tissue inflammation, and therefore lower foreskin susceptibility to HIV.

## Antimicrobial modification of the penile microbiome may reduce HIV risk

Modification of the penile microbiota composition, specifically a reduction in genital anaerobes, might therefore reduce foreskin tissue inflammation and constitute a novel, low-tech avenue for HIV prevention in men at risk of HIV who do not wish to be circumcised [8]. However, it is not known which antimicrobial agents (if any) can optimally modify the penile microbiota, or whether penile microbiota alterations will reduce foreskin inflammation and HIV susceptibility. This proposed clinical trial will examine the effect of microbiota-targeted interventions on foreskin HIV susceptibility. Specifically, male participants will be provided with commonly available, licensed antibacterial agents prior to elective penile circumcision. Genital swabs and tissues collected at the time of PC will then be tested to assess the impact on foreskin microbiota, immune parameters and cellular HIV susceptibility. Therefore, the primary goal of this clinical trial is to translate prior basic science research into low-tech, affordable interventions that can reduce HIV risk in uncircumcised men identifying themselves as heterosexual, and extend our understanding of penile immunology and HIV susceptibility.

## Methods/design

### Study design and site

This study is an open-label, randomized clinical trial assessing the effect of common antibacterials on foreskin HIV susceptibility, immunology, and microbiota composition. The study is being conducted at the Uganda Virus Research Institute (UVRI)–International Aids Vaccine Initiative (IAVI) and Entebbe General Hospital in Entebbe, Uganda.

### Study population

A total of 125 HIV-negative Ugandan men will be enrolled. Eligible men are aged ≥ 18 years seeking voluntary PC at Entebbe General Hospital in Uganda. Men will be invited to participate in the study during the health education and HIV counseling/testing sessions routinely held at the clinic. If men are in a stable heterosexual relationship, their female partners will also be eligible for participation in the study.

### Study treatment groups and randomization

Eligible men (Table 1), who have provided informed, written consent to participate in the trial, will self-randomize, in a computer-generated, open-label fashion to any of the study groups. The study enroller randomly shuffles a pile of sealed, opaque envelopes in the presence of the participant, who then picks a single envelope from the pile. Inside the envelope are details about the participant’s randomization to one of the five study groups (*n* = 25 participants per group), as follows: group 1 is the no treatment (control) group which undergoes immediate PC, as per the normal Entebbe General Hospital protocol; in group 2, participants defer PC for 4 weeks and are provided with tinidazole 2 g by mouth once daily for 2 days (this imidazole class is indicated for treatment of several conditions including amebiasis, giardiasis, trichomoniasis and bacterial vaginosis [17, 18]); in group 3, participants defer PC for 4 weeks and apply topical metronidazole cream 0.75% underneath the foreskin twice daily for 1 week and then twice weekly for the remaining 3 weeks (this topical imidazole is indicated for treatment of bacterial vaginosis [18]); in group 4, participants defer PC for 4 weeks and apply topical clindamycin 2% cream underneath the foreskin twice daily for 1 week and then twice weekly for the remaining 3 weeks (this topical antibiotic is indicated for treatment of bacterial vaginosis [18]); in group 5, participants defer PC for 4 weeks and apply topical hydrogen peroxide 1% gel underneath the foreskin twice daily for 1 week and then twice weekly for the remaining 2 weeks (hydrogen peroxide preparations are indicated for topical treatment of gingivitis/periodontitis [19, 20]). Men in intervention groups 3, 4, and 5 will be reminded about product use twice a week via a telephone call.

**Table 1 Tab1:** Inclusion and exclusion criteria

Inclusion criteria	
Aged ≥18 years	
Male	
Uncircumcised	
HIV-negative	
Willing to give written informed consent	
Willing and able to answer a short social-behavior questionnaire	
Willing to comply with study protocol requirements including randomization and study drug usage	
Available for planned duration of randomization group	
Exclusion criteria	
HIV-infected	
Already circumcised	
Self-reported or physician-noted genital itching/burning, penile discharge, genital ulceration or other possible sexually transmitted infection symptoms	
Participating in other research studies that might compromise the outcomes of this study.	

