### Study follow-up and procedures

Potential study participants will be screened for eligibility (Table 1), confirmed to be generally healthy and without symptomatic genital infections, and then consented by study team clinical staff. Any person with sexually transmitted infection (STI) symptoms at screening, including genital ulceration, urethral discharge or dysuria, will be offered syndromic STI treatment as specified by the Uganda Ministry of Health guidelines and enrolment will be deferred; in addition, any participants found to have asymptomatic gonorrhea or chlamydia upon later polymerase chain reaction (PCR) urine screening will be provided with appropriate treatment. HIV counseling, condom provision, and rapid HIV testing are performed, a social-behavioral baseline questionnaire is administered, and the participant is randomized. Biological samples collected include peripheral venous blood, a first void urine specimen, and genital tract swab samples from the coronal sulcus, inner foreskin, and urethral meatus. All male participants will receive tetanus toxoid vaccination as recommended by the Uganda Ministry of Health guidelines prior to PC. Participants in group 2 have a post-treatment visit on day 3, and those in groups 3–5 on day 8. Men in intervention groups 3, 4, and 5, will be reminded about product use twice a week via a telephone call. After 4 weeks, men are interviewed about product use, tolerability, and sexual practices, provide a repeat blood sample and penile swabs, and undergo routine PC. The excised foreskin tissues are used for immune-based assays to assess the HIV susceptibility of foreskin-derived CD4^+^ T cells (see below). Participants are deemed lost to follow-up if they do not return within 3 days of a scheduled date/visit (see Fig. 1 for visit scheduling).

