While the penile microbiota may be a central determinant of HIV risk, it is not known whether and/or in what way common antimicrobials will alter the composition of the foreskin microbiota. In addition, it is an important point of principle to demonstrate that such changes, once induced, can alter local tissue immunology and HIV susceptibility. Therefore, this randomized, open-label clinical trial aims to establish the impact of four widely available, cheap, and well-tolerated antimicrobials on foreskin immunology, HIV susceptibility, and microbiota. While not intuitively a major concern, a prespecified subanalysis will assess the safety and immune/microbial effects of male penile antimicrobial use in the genital tract of long-term female partners, if applicable. One strength of the proposed approach is that the antimicrobials being investigated are generally low-cost, already licensed for use in Uganda, and have demonstrated efficacy against bacterial vaginosis, a condition that is mediated by several bacterial species also linked with penile inflammation and HIV susceptibility [14, 16]. However, should any product be demonstrated to favorably alter the penile microbiota and/or HIV susceptibility, important future questions for study would include the time course and duration of these changes, longer-term participant acceptability of product application, and the long-term potential for side effects or antibiotic resistance.

Our primary endpoint is the impact of each clinical intervention on HIV entry into foreskin-derived CD4^+^ T cells, compared with the no-intervention group. In addition to these four primary endpoints, we will be assessing multiple secondary endpoints, both immunological and microbiological, meaning that some statistically significant associations found may be due to chance alone. Our sample size does not permit us to rigorously control for multiple comparisons. However, since no prior studies have assessed the ability of a microbiome-based intervention to reduce penile HIV susceptibility, all trial outcomes other than tolerability will be primarily treated as hypothesis generating, with the goal of identifying 1–2 clinical approaches to take forward into more rigorous clinical testing.

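### Group 5's gel schedule adds up to 3 weeks against a 4-week deferral, so read literally its foreskin is taken at least 7 days after last use

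*Protocol article*

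**What the plan says.** Under Study treatment groups and randomization, the protocol article sets the same deferral for every active arm; for the peroxide arm it reads "in group 5, participants defer PC for 4 weeks". The dosing instruction for that arm is to "apply topical hydrogen peroxide 1% gel underneath the foreskin twice daily for 1 week and then twice weekly for the remaining 2 weeks".

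The metronidazole arm (group 3) is to "apply topical metronidazole cream 0.75% underneath the foreskin twice daily for 1 week and then twice weekly for the remaining 3 weeks", and the clindamycin arm (group 4) has the same timing, ending "twice weekly for the remaining 3 weeks".

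The surrounding text treats the three topical arms alike:

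- The abstract says that "the four intervention groups will defer PC for 1 month".
- On reminders, "Men in intervention groups 3, 4, and 5 will be reminded about product use twice a week via a telephone call".
- Study follow-up and procedures puts groups 3 to 5 on the same day-8 visit. It then gives all deferred arms one set of week-4 procedures, beginning "After 4 weeks, men are interviewed about product use, tolerability, and sexual practices" and ending with circumcision.
- Statistical analysis describes the later samples from the intervention arms as taken at on-product visits.

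**The concern.** The group 5 instruction contradicts itself. After one week of a four-week deferral, three weeks remain, not two. A reader cannot tell whether gel use was meant to run up to circumcision or to stop a week before it.

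This matters because the primary endpoint, pseudovirus entry into foreskin CD4+ T cells, is measured on the tissue removed at week 4. Read literally, the group 5 contrast with control estimates an effect that has persisted for a week or more after the gel stops, while groups 3 and 4 are sampled during use. If the anaerobes recover quickly, a product that works during use could look inactive. The Discussion itself leaves the time course and duration of any change as a question for later study, so a one-week gap cannot be assumed harmless.

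The trial's stated goal is to choose one or two "clinical approaches to take forward into more rigorous clinical testing". That choice will in practice set the arms side by side even though no test between products is planned.

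**Working it through.** **Inputs** (protocol article, Study treatment groups and randomization, and Study follow-up and procedures)

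- Deferral in groups 2 to 5: 4 weeks = 28 days.
- Groups 3 and 4: twice daily for 1 week, then twice weekly for 3 weeks.
- Group 5: twice daily for 1 week, then twice weekly for 2 weeks.
- First visit after the daily phase, groups 3 to 5: day 8. This places the start of dosing at about enrolment in all three arms.
- Arm size: 25.

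**Step 1. Does the schedule fill the deferral?**

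- Groups 3 and 4: 1 + 3 = 4 weeks = 28 days. The stated deferral is reproduced.
- Group 5: 1 + 2 = 3 weeks = 21 days. It is not reproduced; 28 − 21 = 7 days are unaccounted for.

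**Step 2. Number of applications**

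- Groups 3 and 4: 7 × 2 + 3 × 2 = 20.
- Group 5: 7 × 2 + 2 × 2 = 18.
- Shortfall: (20 − 18)/20 = 10%.

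The dose difference is small. The timing is what matters.

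**Step 3. Time from last use to circumcision**

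Take circumcision on day 28 and unbroken dosing from enrolment. The last possible day of gel use in group 5 is day 21 if dosing starts on day 1, or day 20 if it starts on day 0. The gap is then 28 − 21 = 7 or 28 − 20 = 8 days, so at least 7.

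Twice-weekly dosing need not fall on the final day. Assume the last dose comes 0 to 4 days before the end of the final dosing week (my assumption; the article does not fix the days), with dosing weeks ending on days 21 and 28:

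| Arm | Calculation | Days since last use |
|---|---|---|
| Groups 3 and 4 | 28 − 28 + (0 to 4) | 0 to 4 |
| Group 5, as written | 28 − 21 + (0 to 4) | 7 to 11 |
| Group 5, if 3 weeks was meant | 28 − 28 + (0 to 4) | 0 to 4 |

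On this assumption the two ranges do not overlap.

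**Step 4. Sensitivity to visit timing**

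The follow-up section counts a man as lost if he does not return within 3 days of a scheduled visit. That rule defines loss to follow-up and does not schedule early surgery. If circumcision did move by 3 days, then with gel used on the last possible day the group 5 gap would be 25 − 21 = 4 or 25 − 20 = 5 days when early, and 31 − 21 = 10 or 31 − 20 = 11 days when late.

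**Step 5. Does other text explain a gap?**

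None of the text shown does. The deferral, day-8 visit, reminder calls and week-4 procedures are common to the topical arms, no washout is mentioned, and the analysis section's description of the follow-up samples points against one. The day-8 samples are unaffected under either reading.

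**The case against.** The strongest reply is that this is a one-word slip. The word remaining refers to the rest of the deferral, which is three weeks after week 1, so the sentence does not define a washout. If three weeks was meant, the gap, the rebound concern and the change in what is estimated all disappear. This is probably right about intent, but it is a reason to correct the text, because the published dosing rule still gives the wrong figure.

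Second, time since last dose already differs between arms by design. Group 2 takes tinidazole for 2 days and is circumcised at 4 weeks, about 28 − 2 = 26 days after its last dose. Rebound applies more strongly there, and the trial never had a uniform on-product comparison across all four active arms. This stands, and it tempers the comparability argument. The difference is that group 2's off-drug interval follows plainly from its stated course, whereas group 5's arises only from a contradiction.

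Third, each product is tested only against control, and the Discussion treats every outcome except tolerability as primarily exploratory. Error rates, power and sample size are untouched. This also stands: the consequence is for the interpretation of one contrast.

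Finally, the schedule figure (Fig. 1) and the full protocol are not shown and may give the right schedule. The article therefore cannot show what participants were actually told. That limits the claim to the text as written; it does not reconcile that text.

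**Conclusion.** The concern holds. As written, group 5's dosing covers 21 of the 28 days before circumcision, and nothing in the text shown explains the missing week. It affects one of four active arms (25 men) and only the week-4 samples, which include the primary endpoint.

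The 7-day minimum rests on dosing from enrolment without a break and circumcision at the nominal 4 weeks; the upper figure of 11 days also rests on the assumed spacing of twice-weekly doses. The consequence for interpretation is conditional: it arises only if gel really stopped at week 3. Even then the contrast with control is valid for the regimen given, but it answers a different question from groups 3 and 4. This should be fixed. It does not threaten the validity of the trial.

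**What to change.** Check the schedule given to participants.

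- If gel was to be used until circumcision, change group 5's second phase to 3 weeks, which restores 28 days and 20 applications.
- If gel does stop at week 3, state the one-week gap and its reason. Interpret the group 5 week-4 results, including the primary endpoint, as an effect after stopping, and do not describe those samples as on-product.

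Under either reading, report days from last product use to circumcision by arm, including group 2, so that differences between arms can be read against time off product.

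The cost is a text correction and one derived variable, with no new visit or sample. The week-4 interview already covers product use; the article does not say that the date of last use is recorded, so this may need one added question.

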### Study outcomes

The broad objectives of this clinical trial are: 1) to quantify the impact of antimicrobial agents on foreskin HIV susceptibility, immunology, and microbiota; and 2) to assess the potential impact of male partner antimicrobial use on the genital immunology and microbiota in their female sexual partner. The primary study endpoint is the percentage HIV pseudovirus entry into foreskin-derived CD4^+^ T cells in the intervention versus control arms, utilizing a validated primary clade A, R5 tropic pseudovirus entry assay [21, 22]. Secondary study endpoints include: 1) foreskin tissue density of HIV-susceptible CD4^+^ T cells; 2) the density and percentage of CD4^+^ T cell subsets (including Th17 cells) in foreskin tissue; 3) the density of Langerhans cells in foreskin tissue based on immunofluorescence microscopy; 4) the presence of foreskin inflammation using cytokine/chemokine quantitation assayed by enzyme-linked immunosorbent assay (ELISA), defined as the presence of ≥ 3/7 inflammatory cytokines within the top quartile for that cytokine; 5) foreskin microbiota composition as characterized using 16S rRNA sequencing; and 6) foreskin tissue explant HIV susceptibility, based on p24 ELISA after ex vivo incubation with a primary HIV isolate.

### Study follow-up and procedures

Potential study participants will be screened for eligibility (Table 1), confirmed to be generally healthy and without symptomatic genital infections, and then consented by study team clinical staff. Any person with sexually transmitted infection (STI) symptoms at screening, including genital ulceration, urethral discharge or dysuria, will be offered syndromic STI treatment as specified by the Uganda Ministry of Health guidelines and enrolment will be deferred; in addition, any participants found to have asymptomatic gonorrhea or chlamydia upon later polymerase chain reaction (PCR) urine screening will be provided with appropriate treatment. HIV counseling, condom provision, and rapid HIV testing are performed, a social-behavioral baseline questionnaire is administered, and the participant is randomized. Biological samples collected include peripheral venous blood, a first void urine specimen, and genital tract swab samples from the coronal sulcus, inner foreskin, and urethral meatus. All male participants will receive tetanus toxoid vaccination as recommended by the Uganda Ministry of Health guidelines prior to PC. Participants in group 2 have a post-treatment visit on day 3, and those in groups 3–5 on day 8. Men in intervention groups 3, 4, and 5, will be reminded about product use twice a week via a telephone call. After 4 weeks, men are interviewed about product use, tolerability, and sexual practices, provide a repeat blood sample and penile swabs, and undergo routine PC. The excised foreskin tissues are used for immune-based assays to assess the HIV susceptibility of foreskin-derived CD4^+^ T cells (see below). Participants are deemed lost to follow-up if they do not return within 3 days of a scheduled date/visit (see Fig. 1 for visit scheduling).

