### Urine collection and handling

First-void urine is self-collected in a urine container and transported on ice to the laboratory where it is aliquoted into a PCR urine tube (Cobas^®^, Roche Molecular Systems, Inc.) prior to later *Neisseria gonorrhoeae* and *Chlamydia trachomatis* testing by PCR.

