### Statistical analysis

The impact of antimicrobial agents on a clade A HIV pseudovirus entry into foreskin-derived CD4^+^ T cells (the primary endpoint) will be assessed by comparing each product group with the untreated control group, using a standard *t* test. The same statistical approach will be used for secondary immune endpoints listed above. The readout for explant HIV infection assays will be the median quantity of HIV p24 antigen produced, and the endpoint will be the percent change in infectivity compared with the vehicle control from the same foreskin, where percentage reduction = ((control − intervention)/control) × 100. A one-sample Wilcoxon-rank test will be used to determine significance (taken as *p* < 0.05). For participants in the intervention groups, the penile bacterial load, microbiota composition, and prepuce cytokine levels will be compared between baseline and on-product visits using a paired *t* test. In female participants, cervico-vaginal bacterial load, microbiota composition, and cytokine levels will be compared between the baseline and follow-up visit using a paired *t* test. In addition, for longitudinally assessed parameters, we will perform an analysis of covariance comparing each intervention group to the control group after adjustment for baseline differences. In case of reported product noncompliance, all participants with missing data will be analyzed according to the group to which they were randomized.

Differences in microbiota biodiversity will be assessed using two biodiversity metrics: diversity (D), calculated as D = Simpson’s diversity index, and evenness (E), calculated as E = D/S, where S is richness. Evenness reflects the dominance by many (i.e., high evenness) versus few (i.e., low evenness) operational taxonomic units (OTUs), whereas richness is a measurement of the total number of unique OTUs present [28]. Differences in overall microbiota composition will be assessed visually based on family-level log-transformed absolute abundance data using nMDS and Bray-Curtis distance; differences are assessed using permutational multivariate analysis of variance (PerMANOVA) based on the log-transformed abundance data [29–31].

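### Men in the deferred arms may be treated for asymptomatic gonorrhea or chlamydia before foreskin sampling while immediate-circumcision controls essentially cannot, so part of an apparent product effect could be STI treatment; the size is unknown and probably modest

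*Protocol article*

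**What the plan says.** All places are in the protocol article.

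- **Eligibility** (Table 1, under Study treatment groups and randomization). The STI-related exclusion rests on symptoms and signs: "Self-reported or physician-noted genital itching/burning, penile discharge, genital ulceration or other possible sexually transmitted infection symptoms". A man with a silent infection can enrol.
- **Testing and treatment.** Under Urine collection and handling, first-void urine is aliquoted "prior to later *Neisseria gonorrhoeae* and *Chlamydia trachomatis* testing by PCR". Under Study follow-up and procedures, "any participants found to have asymptomatic gonorrhea or chlamydia upon later polymerase chain reaction (PCR) urine screening will be provided with appropriate treatment". No turnaround time is given and no arm is exempted.
- **Timing of circumcision** (Study treatment groups and randomization). For controls: "group 1 is the no treatment (control) group which undergoes immediate PC, as per the normal Entebbe General Hospital protocol". For the first product arm: "in group 2, participants defer PC for 4 weeks and are provided with tinidazole 2 g by mouth once daily for 2 days". Groups 3-5 have the same 4-week deferral.
- **Endpoint.** According to the abstract, HIV entry into foreskin CD4+ T cells "will be quantified ex vivo at the time of PC using a clade A, R5 tropic HIV pseudovirus assay (primary endpoint"). The tissue is therefore taken at once in controls and after 4 weeks in the product arms.
- **Analysis** (Statistical analysis). The effect on the primary endpoint "will be assessed by comparing each product group with the untreated control group", with a standard t test. Analysis of covariance is planned only for parameters measured longitudinally. The excised foreskin has no baseline value, so entry is not among them.

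**The concern.** Only the product arms have an interval between enrolment and tissue sampling, and in that interval a man with a positive PCR can receive treatment that is not part of the study. A positive control is, in all likelihood, sampled before his result can be acted on. The co-intervention therefore goes with assignment to any product, and randomisation does not balance it because it arises after randomisation.

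The trial asks whether antimicrobials lower foreskin inflammation and, through it, HIV susceptibility. STI treatment, presumably antibiotic, is an extra antimicrobial exposure that could act on the same pathway. Any resulting bias would favour all four products against one shared control group, so similar results across the products would not reveal it. The trial is meant to choose one or two approaches to take forward, using a reduction of at least 33% as the bar, and a shared bias would bear on that choice.

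**Working it through.** **Step 1. Does the asymmetry follow from the text?**

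| | Control | Groups 2-5 |
|---|---|---|
| Silent infection allowed at entry | yes | yes |
| Urine PCR, treated if positive | yes, result later | yes, result later |
| Time from enrolment to tissue sampling | none stated (immediate) | 4 weeks |
| Treatment possible before sampling | essentially no | yes, if the result returns within 4 weeks |
| Allowed for in the primary test | no | no |

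The possibility follows. Whether it is realised depends on PCR turnaround, which is not stated. The visit schedule (Fig. 1) is not available to check.

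**Step 2. The plan's own figures.** Under Sample size, control entry is 15.1% (median) and the target is a reduction of at least 33%, which is 0.33 × 15.1 = 4.98 percentage points. Power is put at 80% with 25 per group. No SD, alpha or sidedness is given, so the 80% cannot be reproduced. At two-sided 0.05, a t test has 80% power for 4.98 points if the SD is 6.16. That SD is used below only as a yardstick.

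**Step 3. Size of the possible bias.** The document gives neither of these two inputs, so both are assumptions:

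- p, the proportion PCR-positive at enrolment: 4-12%, or 1 to 3 men in 25.
- r, entry in infected relative to uninfected men: 1.5 to 2.

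Suppose further that every positive man in groups 2-5 is treated before circumcision, that treatment fully reverses the effect, and that the product is inert. With uninfected entry m, the control mean is m × [1 + p(r − 1)] and the product-arm mean is m. The apparent reduction is

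p(r − 1) / [1 + p(r − 1)].

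| p | r | p(r − 1) | Apparent reduction | Share of the 33% target |
|---|---|---|---|---|
| 4% | 1.5 | 0.02 | 0.02/1.02 = 2.0% | 6% |
| 8% | 1.75 | 0.06 | 0.06/1.06 = 5.7% | 17% |
| 12% | 2 | 0.12 | 0.12/1.12 = 10.7% | 32% |
| any | 1 | 0 | 0% | 0% |

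If all results return after circumcision, the reduction is 0% in every row. If half the positives are treated in time, it is halved; at the top row of values that gives 0.06/1.12 = 5.4%.

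**Step 4. Effect on the test.** Take a control mean of 15.1, an SD of 6.16 and 25 per group, with p = 5%. As infection raises entry by 33% to 100%, the bias is 0.25 to 0.72 points, and the nominal two-sided 5% error becomes 5.2% to 6.9%. At a more extreme p = 15% with doubled entry, the bias is 1.97 points and the error 19.8%.

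**Step 5. Could it carry a product over the 33% bar?** A true 25% reduction reads as 1 − 0.75/[1 + p(r − 1)]. To reach 33%, p(r − 1) must be at least 0.75/0.67 − 1 = 0.119.

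- At p(r − 1) = 0.02: 1 − 0.75/1.02 = 26.5%.
- At 0.06: 1 − 0.75/1.06 = 29.2%.
- At 0.12: 1 − 0.75/1.12 = 33.0%.
- At 0.12 with half the positives treated in time: 1 − 0.75 × 1.06/1.12 = 29.0%.

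Only the extreme corner of the assumed range reaches the bar.

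**The case against.** Four objections have weight.

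1. **Timing is not stated.** Testing described only as later fits batch testing after the study visits as well as it fits results within the 4 weeks. In the first case no man is treated before sampling and the bias is zero. This stands, and it makes the point conditional.

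2. **The mechanism is not in the document.** The article links foreskin inflammation to anaerobic bacteria. It does not say that asymptomatic gonorrhea or chlamydia found in urine changes the percentage of foreskin CD4+ T cells that the virus enters. This stands too: r is an assumption, and r = 1 is possible. A reader might infer that the plan is shown to have a biased primary comparison, or that a 25% effect would pass as 33%. The document supports neither. The second needs the most unfavourable prevalence and infection effect in the assumed range, every positive treated in time and full reversal.

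3. **Dropping men from the primary analysis has a price.** A reader might conclude that PCR-positive men should leave the primary set. The article analyses men as randomised and bases power on 25 per group. With the yardstick SD of 6.16, losing 1 to 3 men per arm lowers power from 80% to about 78-75%, and the population becomes PCR-negative men. This stands, and the fix leaves the primary analysis alone.

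4. **This is detail for the full protocol or SAP, and the trial is hypothesis-generating.** This holds only in part. Analysis sets and antibiotic logs may well be specified elsewhere. But the imbalance comes from design features that the article does state: immediate against deferred circumcision, with treatment of positives in between. The primary test that it states does not address them. An exploratory trial still uses its results to choose which products to develop further.

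**Conclusion.** The point holds as a possibility that the stated design leaves open. Treatment of asymptomatic gonorrhea or chlamydia can precede tissue sampling in groups 2-5 and essentially cannot in controls, and the unadjusted primary comparison does not separate it from the product effect.

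The size is unknown and probably modest: about a 2-11% apparent reduction, against a 33% threshold. That range rests on assumed prevalence of 4-12%, an assumed 1.5-2-fold effect of infection on entry, treatment of all positives before deferred circumcision, and full reversal. It falls to zero if results come back after circumcision, or if infection and its treatment leave entry unchanged. The documents show neither that the bias occurred nor that it would by itself carry a product over the threshold. They do give the trial the data to check, because the urine tests are already planned.

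**What to change.** - Keep the comparison of all randomised men as the primary analysis.
- Prespecify beside it the same comparison after excluding, in all five arms, men whose enrolment urine is PCR-positive for *N. gonorrhoeae* or *C. trachomatis*. The exclusion uses a sample taken before any product could act, so it does not break the randomised comparison. This requires that enrolment urine is tested in every arm, controls included.
- Report by arm the number PCR-positive, and the date and agent of any non-study antibiotic relative to circumcision. If no man was treated before sampling, that table alone settles the matter.
- Require the two analyses to agree before attributing an effect to a product. Judge agreement on the estimates and their intervals, since the companion analysis is slightly smaller and its p value will move for that reason alone.

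The cost is one sentence on the companion analysis and one case-report field. The companion analysis loses some precision, about 1-3 men per arm under the assumptions above. Treatment of positive men is unchanged.
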